## Abstract

BACKGROUND: The Physical Literacy in the Early Years (PLEY) intervention is a randomized mixed-methods controlled trial focused on embedding loose parts materials into the outdoor play spaces of regulated child care centres across Nova Scotia. The aim is to evaluate the efficacy of the PLEY intervention versus standard regulated childcare practice in influencing thoughts and behaviors of children, parents, and educators. METHODS: Participating early child care centres (n = 19) were randomly assigned to intervention or control sites. Intervention sites received loose parts kits at the beginning of the project while control sites received kits upon project completion. The kits included items such as rocks, tree cookies, balls, wood planks, tubes, tires, ropes, and pulleys. Children (n = 183 at baseline) had their physical activity (accelerometers) and movement skills (TGMD-3 and PGMQ) measured before and after the intervention. All centres provided responses to environmental surveys (Go NAP SACC and Site Context Questionnaire), and educators in intervention sites participated in focus group and photovoice sessions. Educators were also provided with a full day professional development opportunity (plus ongoing mentoring) focused on physical activity, physical literacy, outdoor play, risk-taking, and loose parts. Parents participated in an interview addressing active outdoor play, physical literacy, and attitudes towards risk taking during play. DISCUSSION: This study will provide a better understanding of how integrating loose parts materials into outdoor play spaces impacts children’s health, and the impact on educator and parent attitudes, beliefs, and understanding around physical literacy, active outdoor play and risk-taking during play.

## 1. Introduction

Physical activity (PA) participation in the early years (age 0–4 years) and in school-aged children and youth (age 5–17 years) is associated with a wide range of physiological, psychological and socio-emotional health benefits that can track into adulthood, and importantly, contribute to a decreased risk of chronic disease [1]. Several systematic reviews demonstrate favorable associations of PA with motor skill development, adiposity, fitness, bone and skeletal health, psychosocial and cardio-metabolic health, and cognitive development [1,2,3,4]. A recent review, including 96 studies representing 71,291 children from 36 countries, suggested the more PA, the better (in terms of health benefits) for young children (age 0-4 years), with moderate-to-vigorous physical activity (MVPA) and total physical activity consistently favorably associated with health benefits [4]. Limiting sedentary behavior (SB), particularly screen time [5] and attaining optimal levels of sleep (quality and quantity) [6] are also critical for healthy growth and development during the early years.

While these movement behaviors are often studied in isolation in relation to health outcomes in childhood, emerging evidence is showing that they interact with one another to impact children’s health [7,8,9]. Kuzik and colleagues’ recent systematic review of the relationships between combinations of movement behaviors and health indicators in the early years (age 0–4 years) illustrated that the most ideal combination of PA and SB were favorably associated with motor development and fitness in preschoolers. Comprehensive 24-h movement guidelines are now available for the early years [10] and school-aged children and youth [11]. These guidelines outline a whole day approach to movement and highlight the importance of maintaining health behaviors (PA, sleep and limited SB) across a child’s day. According to these guidelines, preschool-aged children (age 3–4 years) should spend at least 180 min per day engaged in a variety of PAs (structured and unstructured), of which at least 60 min is energetic play; with more PA being better [10]. Preschoolers should not be restrained for more than one hour at a time or sit for extended periods; sedentary screen time should be no more than one hour/day (less is better); and when sedentary, engaging in reading and storytelling is encouraged. It is also recommended that preschool-aged children obtain 10 to 13 h of quality sleep a night, maintaining consistent bed- and wake-times [10].

Despite this evidence, Canadian preschoolers spend very little of their waking hours physically active, and more of their time sedentary. Analyses of Canadian Health Measures Survey data (Cycles 2–4: 2009–2011; 2012–2013; 2014–2015), representing 803 children aged 3 to 4 years, revealed that participants were physically active for 4.6 h per day, on average, with approximately one hour spent in MVPA [8]. Just 12.7% of preschoolers meet the 24-h movement guidelines, with a high proportion (61.8%, and 83.9%) meeting the PA and sleep recommendations, respectively, and a minority (24.4%) meeting the screen time recommendations (3.3% of preschoolers met none of the recommendations). Together, these findings, and previous reports [12], suggest that the majority of Canadian children aged 3 to 5 years are spending too much of their day sedentary (particularly in screen-time behaviors) displacing time that could otherwise be spent physically active.

Understanding key influencers of preschoolers’ movement behaviors is crucial to determine how best to support opportunities to be physically active in the early years. Several systematic reviews of correlates and determinants of PA during the early years have identified time spent outdoors [13,14], the preschool setting [15], and motor skill development [2,4] to have a favorable impact on preschoolers’ PA behaviors. Considering the impact that these variables can have within an early years environment, there is an opportunity to emphasize movement exploration and active play in young children, particularly in the outdoor environment.

There is considerable evidence to suggest that children’s opportunities to engage in outdoor play have steadily declined over the past several generations [16,17]. Children spend less time now outside than their parents did [18,19] and there has been a shift from unstructured and unsupervised outdoor play to structured and supervised activities (mostly indoors) [20,21]. The benefits of active outdoor play to children’s healthy growth and development are well established [16,17] with increased attention placed recently on increasing children’s participation in it. The ParticipACTION Position Statement on Active Outdoor Play describes that “access to active play in nature and outdoors- with its risks- is essential for healthy development” and recommends, “increasing children’s opportunities for self-directed play outdoors in all settings—at home, at school, at child care, the community, and nature.” [22].

Social and physical environments have an important influence on the PA, health, and wellbeing of children. Early childhood education and care services can provide social and physical environments that support children’s PA and outdoor play opportunities. In child care centres specifically PA participation is frequently reported to be low [23]. A Canadian study including preschoolers revealed that children spent on average just 1.5 min per hour in MVPA, and 40.6 min per hour sedentary [24]. Given that Canadian preschoolers spend an average of 29 h a week in childcare [25], this environment is critical for encouraging active behaviors. PA interventions in child care settings have demonstrated varying levels of success. Some interventions significantly improved PA behaviors during the preschool day [26]; however, these improvements were not maintained in 6-month or 12-month follow-ups [23]. As such, conducting research in child care settings provides ample opportunity to encourage sustainable change. These findings may suggest that future interventions need to focus on more than just PA, encouraging a more holistic approach to incorporate broader constructs like physical literacy.

The preschool years are seen as opportune for developing fundamental movement skills (FMS) due to children in this age group experiencing rapid brain growth and neuromuscular maturation, as well as high levels of perceived competence [27]. FMS are one component of a more holistic concept, physical literacy, the “motivation, confidence, physical competence, knowledge, and understanding to value and take responsibility for engagement in physical activities for life” [28,29]. Physical literacy development during the early years is critical for establishing lifelong PA participation [30]. This term, and exploration of components of physical literacy (PL), has started to gain traction in early years’ health-related research [31,32], with increasing interest in exploring settings in which physical literacy development can be supported. As there are limited measurement tools currently validated for use in the preschool age group, this study will seek a more holistic approach to physical literacy through the measurement of movement skills and physical literacy, but also through data collection with parents and educators regarding child behaviors, motivations, and confidence toward PA.

To further enhance physical literacy development, it is encouraged that children are provided with the opportunity to explore new movements and environments. One way to encourage this exploration is through active, outdoor play. Children’s opportunity for unstructured and risky play, as discussed in the 2015 ParticipACTION report card, has been limited given the changes to outdoor play spaces and reduced opportunity overall for outdoor play [33]. Incorporating loose parts into the outdoor play environment may pique children’s curiosity and exploration of movement. Loose parts are described as materials that can be moved and manipulated in various ways to encourage creative thinking, and the opportunity for exploration of their environment [34]. These materials can be from the natural environment (leaves, sticks, etc.) or synthetic (rope, buckets, etc.), and can used in the indoor or outdoor environment.

Loose parts provide opportunities for children to enhance their creativity, collaborative behaviors, and cognitive functioning [35]. An important consideration with loose parts is that the materials be open-ended, to allow for unstructured child-led play, and for children to make use of these materials any way they choose. Although the concept of loose parts has existed for many years [34], to the authors’ knowledge, no evidence exists on the efficacy of integrating loose parts materials in centres’ outdoor spaces as a means of improving children’s physical literacy and increasing PA and active outdoor play [36]. Considering the exploratory and open-ended nature of loose parts materials, it is possible that these materials could influence the basic aspects associated with physical literacy, including movement competence, confidence and motivation, and daily behaviors, increasing the likelihood of lifelong PA participation [30].

### Study Objectives

The objectives of this research were to evaluate the efficacy of the loose parts intervention versus outdoor play practice in standard early child care settings to:(1)improve children’s physical literacy, and increase time in PA and active outdoor play;(2)improve educators’ attitudes, beliefs, perceived competency, and intentions towards incorporating the intervention into practice;(3)increase parents’ and educators’ understanding of play in child health and development.

## 2. Experimental Design

### 2.1. The Intervention

The Physical Literacy in the Early Years (PLEY) project is a randomized, mixed-methods, controlled trial focused on improving physical literacy, PA and active outdoor play in Nova Scotia preschoolers aged 3 to 5 years, through the integration of loose parts materials into outdoor play spaces in regulated child care centres. The PLEY project uses a Socio-Ecological approach [37] to address multiple levels of influence such as the intrapersonal, interpersonal, organizational, community, physical environment, and political levels. An internationally recognized socio-ecological framework, the RE-AIM framework (reach, effectiveness, adoption, implementation, and maintenance) [38], is used to examine research translation and dissemination, and evaluate the intervention. The RE-AIM framework evaluates the ‘reach’ to the target population; the ‘effectiveness’ of the intervention; the extent of ‘adoption’ of the intervention in child care centres; implementation; and ‘maintenance’ of the intervention effects. The RE-AIM framework for centre, educator and child levels is highlighted in Figure 1. This framework approach allows for the possibility to inform current policy and practices in Nova Scotia child care centres at the different levels impacted. This trial was retrospectively registered in October 2017 with BioMed Central under the trial registration number ISRCTN14058106.

The PLEY project was developed using an interdisciplinary, multi-sectoral partnership of researchers, practitioners (early childhood educators), government and policy-makers. The practitioner lens is critical to the partnership, as it provides a deeper understanding of the typical processes that take place in child care centres on a day-to-day basis and gives insight into optimal ways in which the intervention and research can be successfully conducted.

The goal of the PLEY project is to encourage and enable early childhood educators to integrate loose parts materials into child care centres’ outdoor play spaces as a means of improving preschoolers’ physical literacy and increasing time in PA and active outdoor play. The intervention is composed of seven components, which are detailed in Figure 2.

### 2.2. Methods and Design

The primary aim of this randomized, mixed-methods controlled study was to evaluate the efficacy of a loose parts intervention versus standard early years settings’ practice to improve children’s physical literacy, and increase time in PA and active outdoor play. The intervention spanned a period of six to eight months. Funding for the project was secured in November 2015, and the study protocol received ethical approval from the Research Ethics Board (REB 2016-3924) in July 2016. Data collection from the 19 participating sites (intervention: n = 11; control: n = 8) took place from April, 2016- September, 2018. This study was registered as a trial with BioMed Central (ID# ISRCTN14058106) in October 2017 and can be found at http://www.isrctn.com/ISRCTN14058106.

#### 2.2.1. Study Design

A total of nineteen (19) child care centres across Nova Scotia (spread across over 240 km) were randomly allocated to either the intervention (n = 11) or control (n = 8) group. The study took a staggered approach to the recruitment of child care centres. Sixteen sites (intervention: n = 8; control: n = 8) were recruited in November/December of 2016 (Phase 1). An additional three intervention sites were recruited in November of 2017, to account for the drop-out of 1 centre in October of 2017, and participant (child) withdrawal. This study adheres to the CONSORT guidelines for randomized trials. Quantitative and qualitative data were collected at baseline, 3 months, and 6 months post-intervention. Quantitative data were collected from 183 participants at baseline through movement assessments and accelerometry. The same assessments occurred at 3 months post intervention and 6 months post intervention. Centres in the intervention group were provided with a loose parts kit to incorporate in their active outdoor play. The other centres were asked to maintain current scheduling of outdoor play and related activities and received a loose parts kit at the end of the intervention. The loose parts kits for the PLEY project intervention were intended for the outdoor environment and included: buckets and lids (variety of shapes and sizes), rope and pulley, tree cookies, milk crates, a package of hose tube, 20+ balls; a variety of sizes and weights, wood pieces, a bread tray, large cardboard tubes, funnels of different sizes, a tarp, 5′ planks, 5′ PVC tubing (4” and 2” diameter), rocks, and tires. The contents of the loose parts kits were determined based on consultation with the existing literature and discussions with early childhood educators to select natural and synthetic loose parts that best suited the purposes of this project.

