Initially, 21 child care centres in Nova Scotia expressed interest in participating in the study and met study criteria. A visit was scheduled with the centres to meet with the director, further discuss the project, discuss and complete a survey, and view/photograph their designated outdoor play space and adjacent spaces if applicable. Two sites were excluded because they were advanced in their use of loose parts for outdoor play. Three other sites were excluded due to a low response rate to the invitation to participate. For efficacy, the minimum required for a centre to be involved was 10 children, and these centres only received parental consent for 3–5 children. This resulted in a final number of 16 centres in the original cohort, and 3 centres in the new cohort participating in the study. All children between the ages of 3 and 5 years attending the involved child care centres were eligible to participate in the intervention or control groups. Only children whose parents provided informed written consent were formally assessed. At the time of data collection, children also had to provide assent to participate in the assessment (e.g., agreeing to wear the accelerometer). Once the initial recruitment phase was complete and it was determined which centres met all the inclusion criteria (16 sites total), baseline data collection for children (movement assessment and accelerometer measurements) was completed in May 2017. The participating centres were then randomly assigned to the control or intervention group through computer based random number selections, based on rural and urban locations dispersed between the two groups. The full breakdown of number of centres and participants can be seen in Figure 3.

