#### 3.2.3. Educator Training Session

The full day educator training session was facilitated with the intervention sites after the baseline movement assessments and accelerometer measurements were completed. Seven of the eight intervention sites in the original cohort attended: 15 participants (13 ECEs and 2 CDs) took part in the training session; and an alternative training session was subsequently delivered to the one site (educator, assistant director and special needs coordinator) unable to attend the regular training session. In the new cohort, two training sessions were offered; 24 attended the first session, 21 attended the second session. Educators (preschool classrooms), support staff and centre directors were introduced to the project team, the goals, the research methodology and most importantly their role. Participants focused on the key components of the PLEY project including physical literacy and fundamental movement skills, active/outdoor play and loose parts, and the benefits of risk-taking in children’s play. This session also allowed for discussion among attendees from different child care centres to share experiences and stories that further informed the session. The training session was delivered through presentations and hands-on activities designed to promote the use of loose parts for active outdoor play, increase educator understanding of the importance of PA for young children, support observation and documentation, and explain the concepts of physical literacy. Educators had the opportunity to evaluate and describe photographs of children exploring loose parts and to “play” with the loose parts in an outdoor space. The loose parts kits were distributed to the intervention sites upon the completion of the training session. The session provided 6.5 professional development credit hours for the educators.

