### 3.4. Data Analysis

Descriptive statistics will be used to describe study participants (children, educators, parents) and participating child care centres. Linear mixed models with a random effect for centre will be used to determine if children exposed to the PLEY intervention had greater increases in physical literacy, PA, and time in active outdoor play, compared to children in the usual care group (control group). The model will include variables from the children’s TGMD-3 scores, PGMQ scores, and physical activity (as determined by accelerometry). The analysis will be approached from an intention-to-treat strategy. One of the primary outcome measures will be physical activity differences between the groups, while secondary outcomes include height, weight, BMI, and age. Additional analyses of the variables may include an analysis of covariance (ANCOVA) to determine differences in TGMD and PGMQ scores, with similar secondary outcomes of height, weight, BMI, and age, and again including a random effect to control for the clustered design. Missing data will be controlled for within the selected models and analyses. Significance level for these analyses will be set a *p* < 0.05.

Educator focus group data, and parent interview data, will be explored using qualitative analyses, to determine whether the intervention improved educators’ attitudes, beliefs, perceived competency, and intentions towards incorporating the intervention into practice; and increased parents’ and educators’ understanding of play in child health and development. These qualitative data will be transcribed and analyzed using NVIVO software to identify emerging themes. Children’s physical literacy and PA data will be examined in comparison with parent survey and interview responses, and educator survey and focus group responses, using a mixed methods approach. Data from the RE-AIM framework analysis and qualitative data emerging from the photo elicitation focus groups with intervention sites will determine the effectiveness of the intervention to achieve desired outcomes. The mixed methods approach will provide a more holistic understanding of the impact of the PLEY intervention on children’s physical literacy. Although the child measures only include some domains of physical literacy (e.g., physical competence and daily behavior) other aspects of the study including educator focus groups allow us to obtain data on the other components of physical literacy.

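### The article says 19 centres were randomised 11 v 8, but it describes one draw over 16 (8 v 8); three later intervention centres make the pooled contrast not demonstrably randomised

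*Protocol article*

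**What the plan says.** Section 2.2.1 of the protocol article says that nineteen centres "were randomly allocated to either the intervention (n = 11) or control (n = 8) group". The Abstract likewise describes all 19 as randomly assigned.

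The same section then splits the 19 into two waves. The first is "Sixteen sites (intervention: n = 8; control: n = 8) were recruited in November/December of 2016 (Phase 1". Of the second it says "An additional three intervention sites were recruited in November of 2017, to account for the drop-out of 1 centre in October of 2017", and it adds the withdrawal of children as a further reason.

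Section 2.2.2 describes one randomisation. Once 16 sites had met the criteria and the children's baseline had been completed in May 2017, "The participating centres were then randomly assigned to the control or intervention group through computer based random number selections", with rural and urban locations spread over the two groups. It names an original cohort of 16 centres and a new cohort of 3, and gives no allocation procedure for the new cohort.

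Section 3.4 plans linear mixed models with a random effect for centre and states: "The analysis will be approached from an intention-to-treat strategy". It mentions neither a restriction to the 16 centres nor a term for cohort or period.

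**The concern.** The article makes a positive claim about the design, that 19 centres were randomised, and its own description of allocation does not support it. This is a conflict between statements in the article, so it is not excused as detail left to a fuller protocol or an analysis plan.

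If the three later centres went straight into the intervention arm, two things follow for a pooled analysis. Three of the eleven intervention centres had no chance of being controls, so randomisation does not protect the contrast against selection of centres. All eight controls also come from the first wave, so any difference between the waves in season, weather, recruitment or type of centre falls on one arm only. Season plausibly matters for outdoor play and accelerometer-measured activity; the parent interviews in Section 3.3.2 themselves ask about changing seasons and weather. A random centre effect allows for correlation within centres. It does not remove a systematic difference between cohorts that is aligned with arm. The p-value and confidence interval would nevertheless be read as those of a randomised comparison.

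**Working it through.** **1. Counts** (Sections 2.2.1 and 2.2.2)

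- Eligible and interested 21, less 2 advanced in loose parts, less 3 with too few consents: 21 - 2 - 3 = 16.
- First wave: 8 + 8 = 16.
- The stated total of 19 is reproduced only by adding the later three: 16 + 3 = 19; intervention 8 + 3 = 11; control 8 + 0 = 8.

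So every control centre belongs to the first wave, and the only draw described covers 16 centres.

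**2. Could the three have been randomised?** Under 1:1 allocation, the chance that all three go to intervention is 0.5^3 = 0.125. The counts alone do not exclude it. Against it, the three were recruited to make up for losses and no second draw is described.

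**3. Calendar** (Sections 2.2, 2.2.1 and 2.2.2)

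- First-wave baseline completed May 2017; intervention of 6 to 8 months. If it began soon after baseline (inferred), it ended between about November 2017 and January 2018.
- The new cohort was recruited in November 2017 and data collection ended in September 2018. A 6-month intervention inside that window starts between about November 2017 and March 2018.

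Overlap with the controls' intervention period is therefore probably small. No new-cohort baseline date is given, so this is not certain.

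**4. Size of the possible bias** (illustration)

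Inputs: 183 children and 19 centres; ICC 0.02 (Section 2.2.2). Equal centre size is assumed.

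- Children per centre m = 183/19 = 9.63.
- Design effect = 1 + (m - 1) x ICC = 1 + 8.63 x 0.02 = 1.173.
- Children per arm: 11 x 9.63 = 105.9 and 8 x 9.63 = 77.1.
- SE of the contrast in SD units = sqrt(1.173 x (1/105.9 + 1/77.1)) = 0.162.
- Weight of the added centres in their arm = 3/11 = 0.273, so bias = 0.273 x S, where S is the cohort shift in SD.
- Two-sided rejection probability under no effect = 1 - Phi(1.96 - bias/SE) + Phi(-1.96 - bias/SE).

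| S (assumed) | Bias (SD) | Actual error of a nominal 5% test |
|---|---|---|
| 0.2 | 0.055 | 6% |
| 0.3 | 0.082 | 8% |
| 0.5 | 0.136 | 13% |
| 1.0 | 0.273 | 39% |

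**5. Cost of restricting to 16 centres**

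Detectable effect at 80% power = (t0.975 + t0.80) x SE, with degrees of freedom = centres - 2 and no losses.

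- 19 centres, 17 df: (2.110 + 0.863) x 0.162 = 0.482 SD.
- 16 centres, 14 df: SE = sqrt(1.173 x 2/77.1) = 0.174; (2.145 + 0.868) x 0.174 = 0.526 SD (unrounded SE).

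About 16 x 9.63 = 154 of the 183 children remain, if centres are of equal size.

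**The case against.** The strongest reply is that non-random placement is inferred. Section 2.2.1 calls the three centres intervention sites at recruitment, but it labels the first wave by arm at recruitment too, although Section 2.2.2 puts their randomisation after baseline. The label alone therefore proves nothing. The staggered addition is openly disclosed, several sections report the cohorts separately, and the flow diagram and any analysis plan are not at hand. All of this stands, and it is why the fix leaves open documenting a second draw. It does not remove the conflict between 19 and 16. Nor can undisclosed detail put a control centre in the new cohort, since all eight controls are accounted for in the first wave.

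The size of S has no basis in the documents, and the weight may be below 0.27. The new cohort supplied 9 of 85 parent surveys (Section 3.3.1). If children followed that share, it would hold 183 x 9/85 = 19.4 children. With the remaining 163.6 split equally, the weight would be 19.4/(19.4 + 81.8) = 0.19. The figures above are illustrations only.

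Some stronger readings are tempting but not supported:

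- **The addition contradicts intention-to-treat.** That principle concerns analysing units as assigned. Recruiting further centres does not exclude the one that dropped out, and the article does not say which arm lost it.
- **More intensive training confounds the comparison.** Section 3.2.3 reports "In the new cohort, two training sessions were offered; 24 attended the first session, 21 attended the second session", against 15 people from seven original sites. Training is part of the intervention, so this is variation in delivery. It is not stated whether the two attendances overlap, and an eighth original site was trained separately.
- **Allocation was known before consent and baseline in the new cohort, or there was no concurrency at all.** The order of events and the dates for that cohort are not given.
- **The whole trial is non-randomised.** The 8 v 8 comparison in the first wave remains randomised and concurrent as described.

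**Conclusion.** The concern holds with this scope. The conflict between 19 centres said to be randomised and one described draw over 16 is certain on the face of the article. That the three later centres were placed without randomisation, and with little calendar overlap with the controls, is the likely reading but an inference. Either way the pooled 11 v 8 contrast is not shown to be randomised, and arm is partly confounded with cohort and season, because the new cohort has no control centre.

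The consequence could be slight or serious. Error rates of 6 to 8% for shifts of 0.2 to 0.3 SD would be a modest distortion, whereas 39% for a shift of 1 SD would not. These figures rest on an assumed S, equal centre sizes, ICC 0.02, a normal reference and no losses. The case for correction does not depend on them: the randomisation statement and the main contrast are both affected, and the remedy is cheap.

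**What to change.** 1. Correct Section 2.2.1 and the Abstract to say that 16 centres were randomised 8:8 and three intervention centres were added later without randomisation. If the three were in fact randomised, describe how and when instead.
2. Define the primary intention-to-treat analysis in Section 3.4 as the 16 centres as randomised, keeping all available data from the centre that dropped out if it was one of them. State which arm it belonged to.
3. Report the three later centres separately. Label any 19-centre analysis as a non-randomised sensitivity analysis. Say there that a cohort term cannot separate cohort from treatment: with no controls in the new cohort, those centres add no treatment information once cohort is adjusted for.

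The cost is wording and an analysis-set definition. The detectable effect at 80% power rises from about 0.48 to about 0.53 SD (t reference, ICC 0.02, equal centre sizes, no losses). Loss of children, or of the dropped centre's follow-up, would raise both figures.
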